##### Motor Activity Log

The Motor Activity Log is administered through a semistructured interview to assess how much and how effectively an individual uses their UE in their home environment. It comprises 2 subscales: the amount of use and the quality of movement, totaling 30 items that evaluate the use of the affected UE during daily tasks. Each item is scored on a 6-point Likert scale from 0 to 5, with higher scores reflecting greater perceived motor function. The scale has been reported to demonstrate both validity and reliability [44,45].

##### Upper Limb Self-Efficacy Test

The Upper Limb Self-Efficacy Test (UPSET) measures patients’ confidence in using their UEs for daily activities. It consists of 20 items rated on an 11-point Likert scale (0=no confidence and 10=high confidence). The UPSET has demonstrated good internal consistency and correlates well with other self-efficacy measures [46].

### Assessment of Outcomes

A blinded assessor unaware of group allocations will conduct baseline and postintervention assessments to prevent bias. The assessor will be trained in standardized assessment techniques and cannot access baseline data during postintervention evaluations.

A single trained assessor will perform all assessments at the respective rehabilitation centers while remaining blinded to group allocation and treatment throughout the study. This assessor will travel between centers to ensure consistent assessment procedures.

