### Recruitment and Randomization

Participants will be recruited from the NASAM. Three NASAM centers will be randomly assigned to 1 of 3 groups: the CIMT combined with the NMES group, the CIMT-only group, or the control group. Due to the specific nature of the therapies and the distinct characteristics of the centers, randomizing individual participants within centers is impractical. A cluster randomization approach will be used to minimize contamination among patients attending the same center. In addition, to minimize the risk of contamination between intervention groups, a cluster randomization approach will be used, wherein health care centers will serve as the unit of randomization. Each participating center will be randomly allocated to 1 of the 3 intervention arms using a computer-generated sequence administered by research personnel not involved in intervention delivery or outcome assessment. This concealed allocation process ensures allocation concealment and methodological rigor. Following randomization, all eligible patients who have experienced a stroke attending a given center will receive only the intervention protocol assigned to that facility. This methodological approach enables consistent intervention delivery within each site while substantially reducing the likelihood of cross-contamination between intervention groups—a critical consideration when evaluating health care provider–delivered rehabilitation protocols with behavioral components.

Eligible participants will provide written informed consent before their involvement in the study. The principal investigator or a trained research staff member not involved in therapy delivery will be responsible for obtaining consent from each participant. This process will take place only after participants have received a comprehensive explanation of the study procedures, ensuring that they clearly understand their involvement and the associated risks and benefits.

Following the informed consent process, baseline demographic information, including the participants’ names, ages, and gender, will be collected. Once demographic data have been obtained, the remaining baseline assessments will be conducted. Throughout the study, the confidentiality of all participants’ personal information and data will be strictly maintained in accordance with established research ethics guidelines and data protection regulations.

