### Blinding

Outcome assessors will be blinded to the group assignments to ensure an unbiased evaluation of the results. However, given the significant differences in the therapies and the nature of the interventions, it is not feasible to blind the therapists or the patients involved in the study. Clinical staff must be aware of the specific therapy they are administering. Therapists will be informed that a study is being conducted on different modalities in other NASAM centers, but no particular details about the treatment regimens or locations will be provided. They will be aware of the treatment regime at their center but are reminded not to disclose this information to other therapists, either within or at different centers.

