### Strengths and Limitations

This trial incorporates several methodological strengths that enhance scientific rigor and clinical applicability. Blinded outcome assessors evaluate all participants using validated instruments spanning the International Classification of Functioning, Disability, and Health framework, ensuring a comprehensive assessment of motor impairment, activity limitations, and participation restrictions. Our standardized intervention protocols, supported by detailed treatment manuals and competency-based therapist training, promote consistent implementation across sites. The pragmatic trial design, conducted within existing rehabilitation centers using available clinical resources, enhances external validity and facilitates future implementation.

We acknowledge specific limitations inherent in our study design. While pragmatically necessary given resource constraints, the single-cluster-per-arm randomization strategy prevents traditional design effect calculations in our sample size calculation. We have addressed this limitation through conservative effect size selection and comprehensive statistical modeling that includes the center as a fixed effect covariate. Our mixed ANOVA approach protects against type I error inflation while maintaining adequate sensitivity for detecting clinically meaningful differences. The absence of long-term follow-up assessments limits our understanding of treatment durability; however, immediate postintervention outcomes will establish the foundation for future longitudinal investigations.

Despite rigorous standardization procedures, therapist-delivered interventions inevitably introduce some variability. We minimize this concern through mandatory competency assessments and structured fidelity monitoring. These mitigation strategies ensure that observed treatment differences reflect intervention efficacy rather than health care provider variability.

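### With one arm per center and on-site testing, assessor blinding of FMA-UE and WMFT is asserted but not protected, and it cannot cover the patient-rated MAL and UPSET

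*Protocol article*

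**What the plan says.** **Allocation.** Under Recruitment and Randomization, "Three NASAM centers will be randomly assigned to 1 of 3 groups", and eligible patients "attending a given center will receive only the intervention protocol assigned to that facility". Table 2 lists one center for each arm. Strengths and Limitations acknowledges the structure, but only for sample size: "the single-cluster-per-arm randomization strategy prevents traditional design effect calculations in our sample size calculation".

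**Assessment.** Under Assessment of Outcomes: "A single trained assessor will perform all assessments at the respective rehabilitation centers while remaining blinded to group allocation and treatment throughout the study". The next sentence adds: "This assessor will travel between centers to ensure consistent assessment procedures". The same section denies the assessor access to baseline data at the exit test.

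**Patients and therapists.** The Blinding section says that "it is not feasible to blind the therapists or the patients involved in the study". Its non-disclosure reminder concerns what therapists tell other therapists.

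**Instruments.** FMA-UE items are scored 0 to 2 and WMFT items 0 to 5, both on observed performance. The MAL is "administered through a semistructured interview to assess how much and how effectively an individual uses their UE in their home environment". UPSET asks patients to rate their own confidence on 20 items from 0 to 10.

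**The claim.** The Methods part of the Abstract has a blinded assessor measuring all four outcome domains, including perceived motor function and self-efficacy. Strengths and Limitations lists as a strength: "Blinded outcome assessors evaluate all participants using validated instruments". No exception is made for the self-reports.

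**The concern.** Two separate problems sit under one label.

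The first concerns the scales that the assessor scores. In an individually randomized trial, a slip that reveals one patient's treatment unblinds one patient. Here center and arm coincide and the assessor works inside each center, so one identifying slip can unblind a whole arm. FMA-UE and WMFT need rater judgement, so a rater who knows the arm may score differently.

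The second concerns the scales that the patient rates. A blinded interviewer does not blind the person who supplies the answer. The hypothesis under Anticipated Findings includes superiority in perceived functional use, which is what the MAL measures. A reader who accepts the blinding statement as written could credit a self-reported gain to blinded evaluation.

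**Working it through.** **1. Do the stated safeguards hide the arm?**

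| Stated safeguard | What it hides | Does it hide the arm? |
|---|---|---|
| Assessor has no baseline data at exit | Earlier scores | No |
| Therapists told not to disclose to other therapists | One center's regimen from other therapists | No; assessor and patients are not mentioned |
| Statement that the assessor remains blinded | – | States the aim, gives no means |

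Possible cues on site are the stimulator at the combined-arm center, therapy sessions in view, a mitt on a patient still in treatment, and patients' remarks. The MAL interview about arm use at home invites such remarks, and the person conducting it also scores FMA-UE and WMFT.

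**2. How far does one cue reach?** The plan's size is 42, or 14 per group. It reproduces: for the within-between interaction with 3 groups and m = 2 time points, λ = f²·N·m/(1−ρ) = 0.25² × 42 × 2/0.5 = 10.5 on 2 and 39 degrees of freedom. Power is 0.803 at N = 42 and 0.769 at N = 39. The correlation ρ = 0.5 is assumed, as the article gives none. This point does not change the sample size.

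One identifying cue at a center reaches 14 of 42 patients, or 33%.

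**3. Illustration: chance of a cue.** Suppose each patient independently reveals the treatment with probability p. The article gives no such figure, so p is an assumption shown over a range. The chance of at least one disclosure among n patients is 1 − (1 − p)ⁿ.

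| p | One given center (n = 14) | Anywhere in the trial (n = 42) |
|---|---|---|
| 1% | 13% | 34% |
| 5% | 51% | 88% |
| 10% | 77% | 99% |

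**4. Illustration: effect on the test.** Suppose there is no true effect, but knowledge of treatment adds b SD to one arm's exit score. With 14 per arm, λ = 14 × (2/3)b²/[2(1−ρ)], which is 9.33b² at ρ = 0.5. Center effects are left out.

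| b (assumed) | λ | Rejection rate of the nominal 5% test |
|---|---|---|
| 0.2 | 0.37 | 7.7% |
| 0.3 | 0.84 | 11.3% |
| 0.5 | 2.33 | 24.1% |

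**5. The patient-rated scales.** This step needs no probability. The article says patients cannot be blinded, and patients supply the MAL and UPSET ratings. Those two outcomes are unblinded by construction, which is two of the four instruments in Table 3.

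**The case against.** The strongest reply is that nothing in the article shows that unblinding occurs. The assessor is stated to remain blinded throughout, and a condensed article may leave room layout, scripts and similar detail to a fuller protocol. This stands, and it rules out the reading that assessor blinding fails as designed. What remains is that on-site testing at single-arm centers is a stated design choice, and that the safeguards the article does name do not conceal the arm.

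A reader might infer that any cue unblinds a center and that cues at two centers unblind all 42. That is too strong. The mitt is described for the CIMT group and not restated for the combined group. If both wear it, it separates CIMT from control but not one CIMT arm from the other. Mitts also belong to the intervention weeks, so a patient at the exit test need not be wearing one. A cue reaches the whole center only if it identifies the treatment and the assessor knows, or works out, that allocation is by center.

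It is also fair to say that assessor-blinded describes the assessor, that the Blinding section is open about patients, and that Table 3 labels the MAL as perceived function. So this is not a flat contradiction. The Abstract and Strengths and Limitations nevertheless extend the claim to all four outcomes, and the stated limitations do not mention blinding.

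Finally, the probabilities and shifts above are assumptions, and the article says nothing about this assessor's expectations. A bias toward the combined arm is possible but not shown.

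**Conclusion.** The point holds in two parts of different strength. For FMA-UE and WMFT, blinding is asserted but not protected: one cue that identifies the treatment can reveal the arm of 14 patients. This is a risk, and its size depends on disclosure rates and rater behavior that the article does not give. For MAL and UPSET the conclusion is definite and needs only the article's own statements: these are ratings by unblinded patients, and the blinded-evaluation claim cannot extend to them.

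The documents do not support ranking MAL and UPSET below the other two on this ground. The article ranks none of its four instruments, and blinding does not settle that order. The change is worth making, but the point does not invalidate the trial.

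**What to change.** **For any exit assessments still to be done:**
- Test in a room at the center without therapy equipment, with no mitt worn during testing.
- Instruct patients and staff not to mention treatment to the assessor.
- Do not brief the assessor on which center runs which arm. The cluster design is public, so this lowers the risk without removing it.
- Record the assessor's guess of arm after each exit test and report the guesses by arm.

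**In all cases, including if testing is complete:**
- Limit the assessor-blinded claim to FMA-UE and WMFT in the Abstract, Strengths and Limitations, and the results paper.
- Report MAL and UPSET as unblinded patient-reported outcomes.
- Add this to the stated limitations.
- Do not present gains on MAL or UPSET alone as blinded evidence of superiority.

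The article is dated August 2025 and its Abstract anticipates results in September 2025, so the first group may come too late; the second does not. The cost is wording, a short script, one form item and a weaker blinding claim. No extra assessor, center or patient is needed.

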### Data Collection and Monitoring

All data will be meticulously recorded on case report forms and verified by the researcher. Raw data will be securely stored and accessible to researchers upon request, with appropriate measures to protect patient confidentiality. The principal researcher will be primarily responsible for ensuring the accuracy, integrity, and timeliness of the data entry process. To protect participant privacy, all files will be secured with passwords and only accessible to authorized research team members.

### Sample Size Calculation

We used the G*Power software (version 3.0.10; University of Düsseldorf) to calculate the required sample size. A mixed model ANOVA, a statistical method used to analyze the effects of interventions over time and between groups, was selected to analyze the interventions’ time, group, and interaction effects. The *F* test (ANOVA repeated measures within and between interactions), a specific type of statistical test used in the mixed model ANOVA, was selected for this analysis. With a study power of 80%, an α level of .05, and an effect size of 0.25 (based on the primary outcomes from a previous CIMT study [47]), a minimum sample size of 42 participants (14 in each group) is required. If a group has more than 14 eligible participants, the first 14 to provide consent will be recruited based on the referral date. This first-come, first-served approach ensures transparency in participant selection while maintaining cluster integrity.

An intention-to-treat analysis, which includes all randomized participants, regardless of their adherence to the protocol or completion of the study, will be implemented for this RCT. Under this approach, all recruited participants will be included in the final analysis regardless of protocol adherence, withdrawal, or discontinuation. For participants who withdraw or discontinue the treatment, their baseline data will be used as exit data in the primary analysis. This conservative approach acknowledges the potential impact of missing data while maintaining randomization integrity. Sensitivity analyses using multiple imputation techniques, which are statistical methods used to handle missing data, will be conducted to assess the robustness of findings against different missing data assumptions. This analytical strategy aligns with CONSORT guidelines for reporting randomized trials and addresses potential selection bias that might occur with complete-case analysis.

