## Results

Funding for this study from RECUKM began in November 2023. Between January 2023 and May 2023, we drafted the initial ethics proposal and hired the research staff. Research ethics applications were submitted to the RECUKM from May 2023 to November 2023. We anticipate publishing the study results in 2025.

This study will evaluate the effectiveness of CIMT combined with NMES, CIMT alone, and conventional neurodevelopmental therapy in rehabilitating UE function in chronic stroke survivors. The findings could enable physiotherapists to develop innovative therapies to promote UE function and assist in identifying the most effective treatments for poststroke UE dysfunction. We hypothesize that CIMT combined with NMES will be more effective than the other 2 therapies in improving UE function among survivors of stroke.

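### The 80% power with 42 participants applies only to the omnibus group-by-time test under favourable conditions, not to the hypothesis that CIMT+NMES beats each other arm, and the chosen effect size cannot make up for clustering

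*Protocol article*

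**What the plan says.** The Sample Size Calculation section names the G*Power procedure for the interaction ("ANOVA repeated measures within and between interactions"). The error rates are set by the words "With a study power of 80%, an α level of .05". The assumed effect size is 0.25, which the section attributes to an earlier CIMT study. From these inputs it concludes that "a minimum sample size of 42 participants (14 in each group) is required". It gives no correlation between assessments and no dropout allowance, and it stops enrolment at 14 per group. In the same section, patients who withdraw have their baseline value used as their final value in the primary analysis.

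The Assessment of Outcomes section has two time points: a blinded assessor "will conduct baseline and postintervention assessments to prevent bias". Recruitment and Randomization assigns three centers, one to each arm.

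The Results section states the hypothesis: "We hypothesize that CIMT combined with NMES will be more effective than the other 2 therapies in improving UE function". Anticipated Findings repeats it against CIMT alone and against conventional therapy.

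Strengths and Limitations says that the one-center-per-arm "randomization strategy prevents traditional design effect calculations in our sample size calculation". On how this was handled, it tells the reader: "We have addressed this limitation through conservative effect size selection", together with modelling that includes center as a fixed effect. It adds that the mixed ANOVA guards against an inflated type I error and keeps enough sensitivity for clinically meaningful differences.

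**The concern.** The powered test and the hypothesis are different questions. An omnibus interaction can be significant solely because both CIMT arms differ from conventional therapy, which says nothing about adding NMES. The protocol presents that added value as the gap in the evidence, and it is the contrast for which no power is given.

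The sample size is also the bare minimum for the omnibus test, so nothing is in hand for dropout or for center effects. The text nevertheless assures the reader that the choice of effect size and the mixed ANOVA deal with clustering. If those statements stand, a non-significant CIMT+NMES versus CIMT result could be taken as showing no added benefit, and a significant omnibus result could be credited to treatment when a center difference produced it.

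**Working it through.** **Inputs.** From the protocol: 3 arms, 14 per arm (N = 42), f = 0.25, α = .05, 2 assessments, one center per arm. Not given, so assumed and varied: correlation ρ between assessments, dropout rate, comparator gain, and the ICC of change between centers. σ is the between-patient SD at one assessment, taken as equal at both.

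**1. Reproducing 42.** For the interaction, λ = f²·N·m/(1−ρ), with df 2 and N−3. With m = 2 and ρ = 0.5, λ = 0.0625 × 42 × 2/0.5 = 10.5 on 2 and 39 df, and power is 80.3%. N = 39 gives 76.9%, so 42 is the smallest multiple of three. Holding f and N, power is 65% at ρ = 0.3, 72% at 0.4, 89% at 0.6 and 96% at 0.7.

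**2. What f = 0.25 means.** With two assessments, each interaction cell effect is half the arm's deviation in mean change, so the SD of the three mean changes is 2fσ = 0.5σ.
- Only one arm differs: SD = D·√2/3, so D = 0.5 × 3/√2 = 1.06σ.
- Arms evenly spaced: SD = D/√6, so D = 0.5 × √6 = 1.22σ between the extremes and 0.61σ between neighbours.

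The SD of the change score is σ√(2(1−ρ)), which equals σ at ρ = 0.5.

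**3. Power for the hypothesis.** For a pairwise t test with pooled residual (39 df, two-sided .05), the noncentrality is d·√(14/2), where d = D/√(2(1−ρ)) for change scores. With baseline adjustment, d = D/√(1−ρ²) on 38 df. CIMT+NMES versus CIMT:

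| Analysis | Evenly spaced, 0.61σ | Only the combination works, 1.06σ |
|---|---|---|
| Change score, ρ = 0.3 (d = D/√1.4) | 27% | 64% |
| Change score, ρ = 0.5 (d = D) | 35% | 78% |
| Change score, ρ = 0.7 (d = D/√0.6) | 53% | 94% |
| Baseline-adjusted, ρ = 0.5 (d = D/√0.75) | about 45% | about 88% |

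Power to beat both comparators, by simulation at ρ = 0.5 without adjustment, is about 35% and 66%. Each contrast is tested at .05. Claiming superiority over both needs no division of α.

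**4. Dropout.** With an assumed 15% loss and change set to zero for those lost (simulation, ρ = 0.5), omnibus power is about 69–71% if conventional-therapy patients do not change. It is about 56–59% if all arms gain a further 1 SD, because zeros then add spread as well as shrinking differences. With completers only, λ = 10.5 × 0.85 = 8.9 and power is about 72%.

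**5. Center effects.** With 14 patients from one center per arm, an ICC in change multiplies the expected between-arm mean square, relative to the residual, by (1 + 13·ICC)/(1 − ICC). With no treatment effect, the unadjusted F test (critical value 3.24 on 2 and 39 df) then rejects too often:

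| Assumed ICC of change | Ratio | Type I error |
|---|---|---|
| 0.01 | 1.13/0.99 = 1.14 | 7% |
| 0.02 | 1.26/0.98 = 1.29 | 9% |
| 0.05 | 1.65/0.95 = 1.74 | 17% |
| 0.10 | 2.30/0.90 = 2.56 | 29% |

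A fixed center term does not repair this. Center and arm are the same variable here, so center-by-time is the same term as group-by-time.

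**The case against.** The strongest reply is that nothing is miscalculated. The section names its test, and 42 is right for that test. That stands, and a reader who infers an arithmetic error would be mistaken. Several other stronger readings also fail:

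- **That 80% requires a correlation of exactly 0.5.** Any higher value gives more power. Silence on the correlation could also be condensation in an article and carries little weight alone.
- **That the pairwise contrasts are hopeless.** The Statistical Analysis section plans covariates that include baseline motor function, which lifts the two scenarios to about 45% and 88%. The neighbouring-arm contrast stays weak, but the range must be shown. Bonferroni-reduced figures would overstate the problem: the protocol plans no such correction, and the claim of beating both does not need one.
- **That baseline carried forward is certain to be the primary method.** Sample Size Calculation says so, but Statistical Analysis makes multiple imputation the main approach and carry-forward the comparison. The two sections need reconciling. Neither restores the information lost to dropout.
- **That a design effect yields a corrected power.** The formula 1 + 13·ICC can be evaluated for assumed ICCs, but with one center per arm no between-center degrees of freedom remain. A power quoted from an effective sample size would describe no valid test, and more patients per center would not remove the confounding.
- **That 0.25 is optimistic relative to its source.** The cited CIMT study is not available here, so this cannot be judged.

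The protocol also openly discloses the missing design effect. What does not stand is its statement that the limitation has been addressed.

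**Conclusion.** The concern holds in this limited form. The 80% is correct for the omnibus interaction given f = 0.25, two assessments, a correlation of at least 0.5, full retention and no center effect. It does not describe the stated hypothesis. At ρ = 0.5, power for CIMT+NMES versus CIMT ranges from about 35% to 78% unadjusted, depending on how the arms are spaced.

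The effect size presupposes a largest arm difference of 1.06–1.22 SD, and 42 is the exact minimum for it. It therefore gives no protection against clustering, and the assurances about type I error and sensitivity are wrong as written. The dropout rates, comparator gains and ICCs used here are illustrative assumptions, because the protocol gives none. Severity: should-fix, since the defect lies in what is claimed for the sample size and the remedy is restatement.

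**What to change.** Keep 42 and change the text as follows.

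1. In Sample Size Calculation, say that 42 gives 80% power for the omnibus group-by-time test at f = 0.25 (largest arm difference in change about 1.1–1.2 SD), with two assessments, a correlation of at least 0.5, no dropout and no center effect.
2. Add a small table of power for CIMT+NMES versus each comparator over a range of correlations, with and without baseline adjustment, and one dropout scenario that states the assumed gain in the comparator arm. Make the two sections agree on the primary handling of missing data.
3. In Strengths and Limitations, remove the claims that the effect size addresses clustering, that the mixed ANOVA protects type I error, and that sensitivity is adequate. Say instead that center and treatment effects cannot be separated and that any center effect on change inflates type I error. Illustrate this with assumed ICCs, not with an effective sample size.
4. Present the pairwise contrasts as estimates with confidence intervals, and say that a non-significant CIMT+NMES versus CIMT result will not be read as absence of benefit.

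The cost is wording and one table. No patients are added and no procedures change. The downside is that the stated power looks less favourable.

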### Statistical Analysis

Data will be analyzed using IBM SPSS Statistics software (version 29.0), adhering to the intention-to-treat principle, which includes all randomized participants regardless of protocol adherence. Participant characteristics and baseline measures will be summarized using descriptive statistics, including mean, SD, median, and IQR.

Before primary analyses, data will be assessed for normality using the Shapiro-Wilk test and homogeneity of variance using the Levene test. For outcomes meeting parametric assumptions, a 2-way mixed model ANOVA will be used to compare the effects of the interventions’ interactions between and within groups. Appropriate transformations or nonparametric alternatives will be applied in cases of violated parametric assumptions. Potential confounding variables, such as baseline motor function and stroke severity, will be included as covariates to provide adjusted treatment effect estimates. Statistical significance will be set at *P*<.05 for all analyses.

The linear mixed-effects models that include the center as a fixed effect covariate and random intercepts at the participant level will be used to address residual center-specific effects without invoking a design effect. This modeling framework accommodates hierarchical data structures in single-cluster designs while preserving valid inference for group-by-time interactions.

Missing data will be addressed using multiple imputation techniques, with sensitivity analyses comparing results to those obtained using the baseline observation carried forward method. This comprehensive approach ensures a robust interpretation of intervention effects while preserving statistical power.

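### Two sections give baseline carry-forward and multiple imputation opposite roles, so the leading result is not fixed; the carry-forward trigger is ambiguous and its conservative label is unreliable

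*Protocol article*

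**What the plan says.** The protocol article sets the missing-data rule in two places.

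- **Sample Size Calculation**, second paragraph: "For participants who withdraw or discontinue the treatment, their baseline data will be used as exit data in the primary analysis". Multiple imputation is then the check: "Sensitivity analyses using multiple imputation techniques, which are statistical methods used to handle missing data, will be conducted". The section describes the carry-forward rule this way: "This conservative approach acknowledges the potential impact of missing data while maintaining randomization integrity". The same paragraph states the intention-to-treat principle: "all recruited participants will be included in the final analysis regardless of protocol adherence, withdrawal, or discontinuation".
- **Statistical Analysis**, last paragraph: "Missing data will be addressed using multiple imputation techniques, with sensitivity analyses comparing results to those obtained using the baseline observation carried forward method".

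No sentence says which section governs.

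**The concern.** Each method leads in one section and is the sensitivity check in the other. With 14 participants per arm, a handful of imputed values can move the result. A plan that leaves the lead method open allows the choice to be made after both results are known.

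Two further problems sit in the carry-forward rule itself.

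- **Trigger.** The rule is set off by withdrawing or stopping treatment, not by the absence of an exit score.
- **Label.** Carry-forward sets the change to zero. Where every arm receives active therapy and may improve, that penalises whichever arm has more replaced values. Unequal discontinuation is plausible because the burden differs by design. The CIMT Group section asks for mitt wear for 90% of waking hours on 3 days a week, and Table 2 gives 60 minutes per session in two arms and 60 + 20 in the combined arm. The direction of any imbalance cannot be known beforehand.

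**Working it through.** **1. The two rules side by side**

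| Section | Leading method | Sensitivity method |
|---|---|---|
| Sample Size Calculation | Baseline carried forward | Multiple imputation |
| Statistical Analysis | Multiple imputation | Baseline carried forward |

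This contradiction needs no arithmetic and no assumption.

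**2. The plan's own figure**

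Inputs from Sample Size Calculation: "With a study power of 80%, an α level of .05, and an effect size of 0.25", the test "ANOVA repeated measures within and between interactions", and the result "a minimum sample size of 42 participants (14 in each group) is required". There are k = 3 groups and m = 2 assessments (Assessment of Outcomes). The correlation between assessments is not given, so ρ = 0.5 is assumed.

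- λ = f²·N·m/(1 − ρ) = 0.0625 × 42 × 2/0.5 = 10.5, with df = 2 and 39.
- Power is 0.803 at N = 42 and 0.769 at N = 39. The stated 42 reproduces, and nothing in this point changes it.

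**3. Expected bias under carry-forward**

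If a share d of an arm is replaced and its true gain is g, the expected analysed gain is (1 − d)·g. For arms A and B:

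analysed difference = (1 − d_A)·g_A − (1 − d_B)·g_B

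With equal gains this is (d_B − d_A)·g. For a gain of 0.8 SD, 3/14 replaced in control and 0/14 in the combined arm, it is 3/14 × 0.8 = 0.17 SD against control, with no true difference.

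The same formula in points, with assumed gains:

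| True gains A, B | True difference | Replaced of 14: A, B | Analysed difference |
|---|---|---|---|
| 4, 4 | 0 | 4, 1 | −0.86 |
| 4, 4 | 0 | 1, 4 | +0.86 |
| 4, 4 | 0 | 2, 2 | 0 |
| 6, 3 | 3 | 4, 1 | 1.50 |
| 6, 3 | 3 | 1, 4 | 3.43 |
| 6, 3 | 3 | 2, 2 | 2.57 |

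**4. Rejection rate and power**

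With two assessments, the group-by-time test equals a one-way ANOVA on change scores. This was simulated with unit SD of change, 14 per arm, fixed numbers replaced and independent participants.

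With no true difference and a gain of 0.8 SD in every arm:

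- None replaced: about 4.9% rejection.
- 3/14 in control, none elsewhere: about 6.7% for the three-arm test and about 7.1% for the pairwise comparison of control with the combined arm.
- 2/14 in every arm: about 3.7%, so the test is then conservative.

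For the planned effect, the variance of the three mean gains is 10.5/42 = 0.25. Evenly spaced arms therefore lie √(0.25 × 1.5) = 0.61 SD apart. Two assumed gain levels were used: a mean gain of 0.8 SD across arms (arm gains 1.41, 0.80, 0.19), and 0.8 SD in the lowest arm (2.02, 1.41, 0.80).

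| Replaced of 14 | Power, mean gain 0.8 SD | Power, lowest-arm gain 0.8 SD |
|---|---|---|
| None | 0.80 | 0.80 |
| 2 in each arm | 0.68 | 0.59 |
| 3, best arm only | 0.54 | 0.35 |
| 3, worst arm only | 0.86 | 0.91 |

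As a comparator, dropping 2 patients per arm and analysing the rest gives a power of about 0.73.

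**The case against.** Four points can fairly be made for the plan.

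- **The lead result is not wholly undefined.** A reader might infer that the primary result has no definition. That goes too far: both sections commit to running both methods and comparing them, which limits selective emphasis. The Statistical Analysis section also never calls multiple imputation primary; that role follows from making carry-forward the comparator. What remains open is which analysis leads.
- **Overwriting of real outcomes is a literal reading only.** A reader might infer that the plan discards measured exit scores. It never says so. The sentences after the rule speak of missing data and of complete-case analysis, so the authors may have meant only absent exit scores. The article also does not say whether people who stop treatment are still assessed. What stands is that the trigger, as worded, covers more than missing scores and would conflict with intention-to-treat if applied as written.
- **The false-positive inflation is modest.** In the illustration it reaches about 7%, and equal replacement lowers the rate below 5%. The figures do not support a claim of gross type I error inflation.
- **Not all the power loss is due to carry-forward.** Losing 2 patients per arm already takes power from 0.80 to about 0.73. The extra cost is about 0.05 (0.73 − 0.68) to 0.14 (0.73 − 0.59), depending on the assumed gain. Intervention lasts only 4 weeks, so dropout may be small.

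None of these removes the contradiction between the two sections.

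**Conclusion.** The point holds as a contradiction between two sections of the current text: they assign opposite roles to the same two methods, and nothing resolves it. That alone warrants correction before any outcome is analysed.

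The trigger for carry-forward is ambiguous, and its literal reading conflicts with the intention-to-treat statement in the same paragraph. The conservative label is not reliable. The rule can shrink, enlarge or reverse a difference according to where replacements fall, and only with equal gains and equal replacement is the expected bias zero.

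The sizes (0.17 SD, rejection of about 6.7-7.1%, and power anywhere from about 0.35 to 0.91) are illustrations. They rest on assumed gains, assumed numbers replaced, ρ = 0.5, evenly spaced arms and independent participants. The documents supply no gain or dropout rate, so the figures show what the rule can do, not what will happen in this trial.

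**What to change.** State the same rule in Sample Size Calculation and Statistical Analysis:

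1. Analyse every observed postintervention score in the assigned arm, whether or not treatment was completed.
2. Impute only where the postintervention score is missing. In the carry-forward sentence, remove the reference to stopping treatment.
3. Name one primary method. Multiple imputation with baseline score and arm in the imputation model is preferable; a likelihood-based mixed model is an acceptable alternative, and the article already plans linear mixed-effects models. Arm-specific imputation is not needed and would be fragile with 14 per arm.
4. Keep baseline carry-forward as a sensitivity analysis only, and delete the word conservative.

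The cost is an edit to two paragraphs. Postintervention assessments are already planned, both methods are already in the plan, and N = 42 does not change.
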